### Study workflow

2.3

Upon enrollment (Figure 2), all DoC patients will undergo standardized CRS-R assessments administered at least five times over a one-week period by a trained multidisciplinary team. Scores across all six CRS-R subscales will be documented. Diagnostic classification will be based on the highest level of reproducible behavioral response observed during repeated assessments.

**Figure 2 fig2:**
[figure not shown]
Study workflow the schematic outlines the experimental procedure for assessing EEG responses to rectal stimulation across participant groups (HC, healthy controls; MCS; UWS). Key phases include pre-experiment preparation, rectal stimulation, EEG signal acquisition, and subsequent time-frequency analysis of the event-related potentials (ERPs).

Rectal preparation, EEG setup, rectal catheter placement, stimulation parameters, EEG acquisition, and event synchronization procedures will be conducted as previously described, following standardized safety and comfort protocols. Continuous clinical monitoring will be maintained throughout the procedure. The stimulation will be immediately discontinued if signs of discomfort, autonomic instability, or adverse events are observed. All procedures will be conducted by trained clinical personnel following predefined safety and tolerability criteria, including continuous monitoring of autonomic signs (heart rate, blood pressure, oxygen saturation) and immediate termination of stimulation in case of distress or physiological instability.

### Rectal stimulation and EEG acquisition

2.4

The experimental procedure comprises a preparatory phase and a stimulation phase. Prior to study initiation, written informed consent will be obtained from the legal guardians of all patients with disorders of consciousness (DoC). To minimize potential confounding effects on gastrointestinal motility, medications known to influence gut function (e.g., sedatives, prokinetic agents) will be discontinued for at least 15 days before the experiment, where clinically feasible and under medical supervision.

Before participation, all patients will be jointly evaluated by attending neurologists and gastroenterologists to ensure clinical stability. Inclusion requires stable vital signs, defined as a heart rate of 60–100 beats/min, blood pressure of 90–140/60–90 mmHg, and oxygen saturation of ≥95%.

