### Participant enrollment

2.2

Participants will be recruited according to predefined inclusion and exclusion criteria (Table 1). The target sample size is 15 participants per group: unresponsive wakefulness syndrome (UWS), minimally conscious state (MCS), and age and sex-matched healthy controls (HCs). Written informed consent will be obtained from all participants or, for DoC patients, from their legal guardians prior to enrollment. Healthy control participants will be recruited from the local community and screened to exclude neurological, psychiatric, or gastrointestinal disorders.

**Table 1 tab1:** Inclusion and exclusion criteria for DoC and control individuals.

Patient group inclusion criteria	Patient group exclusion criteria
1. Patients with chronic-phase disorders of consciousness (DoC) (duration ≥28 days) due to etiologies such as traumatic brain injury, stroke, or cardiac arrest.	1. History of developmental psychiatric or neurological disorders causing functional impairment.
2. Age ≥18 years.	2. Untreated epilepsy.
3. Absence of acute complications such as fever or infection within 15 days prior to enrollment.	3. Untreated cerebral edema.
4. No use of sedative medications within 15 days prior to enrollment.	4. Unstable vital signs.
5. No use of any medications potentially affecting gastrointestinal motility within 7 days prior to testing.	5. History of intestinal diseases.
6. Written informed consent provided by family members or legal guardians.	6. History of abdominal surgery, except for simple appendectomy or cholecystectomy.
	7. Presence of organic diseases such as spinal cord injury or thyroid dysfunction.
	8. Patients with skull defects resulting in cranial depression, or those who have undergone cranioplasty with titanium alloy.

Control group inclusion criteria	Control group exclusion criteria
1. Age-matched, conscious healthy adults.	1. Failure to meet any of the above inclusion criteria.
2. No history of gastrointestinal diseases or abdominal surgery.	2. Unwillingness to provide written informed consent.
3. No history of psychiatric disorders.	
4. Cessation of any medications or foods affecting psychiatric or gastrointestinal function 48 h prior to the experiment.	
5. Written informed consent provided by the participant.	

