### Potential risks, burdens, and benefits

3.2

The proposed protocol involves controlled rectal balloon distension combined with EEG recording, which warrants careful consideration of potential risks, participant burden, and anticipated benefits. Rectal distension may induce transient discomfort or mild autonomic responses, such as changes in heart rate or blood pressure. However, the stimulation parameters employed are comparable to procedures routinely used in clinical bowel care for patients with prolonged disorders of consciousness. All procedures will be conducted under continuous bedside monitoring by trained clinical personnel, with predefined stopping criteria and immediate access to medical support to ensure participant safety.

Overall participant burden is considered low. EEG recording is non-invasive and widely used in routine neurological practice, and the rectal stimulation protocol is time-limited and integrated into standard nursing workflows. Importantly, participation in this study will not alter routine clinical management or influence diagnostic or therapeutic decision-making for enrolled patients.

While no direct clinical benefit to individual participants can be expected, the potential scientific and societal benefits are meaningful. By systematically exploring an underexamined dimension of consciousness, this study may provide foundational evidence to inform future research aimed at developing more comprehensive, accessible, and theoretically grounded assessment approaches for DoC. In the longer term and at the population level, such advances may support improved research stratification, more informed prognostic discussions, and the responsible allocation of healthcare resources, in line with public health priorities.

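### Table 1 and section 2.4 set incompatible drug-free rules for patients, and stopping drugs for the experiment contradicts section 3.2's statement that care is unchanged

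*Protocol article*

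**What the plan says.** Section 2.2 recruits participants according to Table 1. Two of the patient inclusion criteria concern drugs:

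- Criterion 4, sedatives: "No use of sedative medications within 15 days prior to enrollment".
- Criterion 5, motility drugs: "No use of any medications potentially affecting gastrointestinal motility within 7 days prior to testing".

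Neither carries an exception.

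Section 2.4 returns to the subject as part of the experimental procedure. It gives the purpose as "To minimize potential confounding effects on gastrointestinal motility", names sedatives and prokinetic agents as examples of the drugs concerned, and says that they "will be discontinued for at least 15 days before the experiment, where clinically feasible and under medical supervision".

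Section 3.2, on risks and burdens, states that "participation in this study will not alter routine clinical management or influence diagnostic or therapeutic decision-making for enrolled patients". The risks it discusses there are those of distension and EEG recording. Drug withdrawal is not among them.

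**The concern.** A site needs one answer to two questions: which recent drug exposure makes a patient ineligible, and whether the study itself causes a patient's drugs to be stopped. The article gives two answers to each.

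The first question affects who is enrolled and how much residual drug exposure can sit in the UWS and MCS groups. Section 2.6 compares those groups with controls by one-way ANOVA for each EEG outcome and describes no adjustment for medication. The limitations in section 3 name medication exposure as something that may influence interoceptive processing.

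The second question concerns safety and consent. These patients cannot consent for themselves, and section 2.9 promises their representatives a detailed account of procedures and risks. That account needs a consistent protocol behind it.

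**Working it through.** The article gives no figure to reproduce. The check sets the rules side by side and compares days. Testing (Table 1) and the experiment (section 2.4) are taken to be the same occasion.

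| Drug class | Feature | Table 1, patients | Section 2.4 |
|---|---|---|---|
| Motility drugs | Length | 7 days | at least 15 days |
| | Counted back from | testing | experiment |
| | Strictness | no exception | only where feasible |
| Sedatives | Length | 15 days | at least 15 days |
| | Counted back from | enrollment | experiment |
| | Strictness | no exception | only where feasible |

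**Motility drugs.** Let d be whole days from last dose to testing.

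- Table 1 is met when d ≥ 8, reading use on day 7 as inside the window.
- The section 2.4 interval is met when d ≥ 15.
- The intervals differ by 15 − 7 = 8 days. For d = 8 to 14, Table 1 is met and the 15-day interval is not, unless the feasibility clause is used.
- For d ≤ 7 in a patient whose drug could not feasibly be stopped, section 2.4 tolerates the exposure and Table 1 excludes the patient.

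So section 2.4 is longer but softer, and neither rule contains the other.

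**Sedatives.** Let t be days from last dose to enrollment and g the days from enrollment to the experiment.

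- Table 1 requires about t ≥ 15. Section 2.4 requires t + g ≥ 15, if feasible.
- The article does not state g. Section 2.3 places at least five CRS-R assessments over one week after enrollment, so I assume g = 0 to 7.
- A patient who just meets Table 1, and receives nothing afterwards, is then 15 + 0 = 15 to 15 + 7 = 22 days sedative-free at the experiment.

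The lengths therefore do not conflict; the anchor and strictness do. A patient enrolled under Table 1 should have no sedative left to stop at enrollment, yet section 2.4 provides for stopping sedatives and for cases where this cannot be done. In the other direction, Table 1 as worded does not reach a sedative given between enrollment and the experiment. Only the conditional rule does.

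**Unchanged care.** Section 2.4 gives a research reason for the discontinuation, namely control of confounding. A drug stopped for that reason is a treatment decision made because of participation. Section 3.2 says participation leads to no such decision. Medical supervision and the feasibility proviso govern how a withdrawal is done and when it is forgone. They do not turn it into usual care.

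**The case against.** The strongest defence is that Table 1 alone decides eligibility and section 2.4 describes preparation, with 7 days as a floor for motility drugs and 15 days as a target. A patient 10 days off a prokinetic at enrollment might well reach 15 days by the test. This is a sensible reading, but the article does not state it or rank the two sections. The 8-to-14-day band is also counted back from testing, so time gained after enrollment is already included. For sedatives the floor-and-target reading does not help, because Table 1 already requires 15 days.

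It is also fair that all group comparisons are declared exploratory (sections 2.5 and 2.7) and that medication exposure is listed as a limitation. Both reduce the inferential harm. Neither tells a site which rule to follow.

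Several stronger readings are tempting and are not supported:

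- **The 48-hour rule as a further contradiction.** "Cessation of any medications or foods affecting psychiatric or gastrointestinal function 48 h prior to the experiment" applies to controls only. It shows that exposure rules differ between patients and controls, but it conflicts with neither patient rule.
- **Sedated patients will be enrolled.** Section 2.4 nowhere says that it waives a Table 1 criterion. Tolerating exposure in one section is not the same as admitting the patient.
- **A known share of exposed patients.** With 15 per group, each exposed patient would be 1/15 = 6.7% of a group, but the documents give no count from which to estimate a share.
- **Exposure confined to patients.** A control could have taken a relevant drug more than 48 hours earlier and still qualify.
- **Guardians are misinformed.** The consent text is not shown. Only the contradiction in the protocol behind it can be seen.

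**Conclusion.** The point holds as an internal inconsistency with two parts. First, the patient drug-free rules differ in length (7 against at least 15 days) and strictness for motility drugs, and in anchor and strictness for sedatives. Second, study-motivated discontinuation is incompatible with the statement that participation leaves management and treatment decisions unchanged. As written, the plan cannot be followed consistently on eligibility or on withdrawal.

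The definite size is the 8-day difference and the resulting 8-to-14-day band for motility drugs. The 15-to-22-day range for sedatives rests on the assumed gap of 0 to 7 days between enrollment and experiment. The effect on the EEG comparisons cannot be quantified, because neither the number of patients affected nor the size of any drug effect is given. The case for correction rests on unclear eligibility, safety, consent and a possible bias of unknown size, not on a demonstrated distortion of results.

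**What to change.** Reconcile Table 1, section 2.4 and section 3.2:

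1. Write one rule per drug class, with one time anchor, used identically wherever it appears.
2. State for each rule whether it is an eligibility criterion or a withdrawal directed by the study, and whether any exception exists.
3. If drugs are withdrawn for the study, correct the section 3.2 statement, add the withdrawal to its risk discussion, and check that the consent text agrees.
4. If any exposure remains permitted, record the drug and the time since last dose, and repeat the group comparisons without exposed participants as a sensitivity analysis.

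The investigators and responsible clinicians decide which interval and rule apply. The cost is an amendment to the wording, a check of the consent text and, if exposure is permitted, one small sensitivity analysis. The sample size and the main analysis do not change.

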#### Bowel preparation and setup

2.4.1

Prior to stimulation, rectal preparation will be performed using standardized protocols. A 60 mL glycerin enema will be administered in the standard condition. For participants with chronic constipation or long-term enema dependence, a combined preparation (20 mL glycerin + 180 mL normal saline) will be used. Following bowel evacuation, a 30-min observation period will be implemented to ensure rectal clearance and physiological stabilization. During this period, the EEG cap will be positioned and impedance optimized.

#### Rectal stimulation paradigm

2.4.2

Gut-related interoceptive stimulation will be delivered using a controlled rectal balloon distension paradigm. A lubricated balloon-tipped catheter (liquid paraffin) will be inserted such that the distal balloon is positioned approximately 10 cm from the anal verge, guided by catheter scale markings. Participants will be maintained in a left lateral decubitus position throughout the procedure.

Stimulation will be administered using a computer-controlled inflation–deflation device developed with participation from the research team, ensuring precise temporal and volumetric control. Each trial will consist of rapid balloon inflation to a fixed volume of 60 mL, reaching target volume within 150 ms, followed by passive deflation.

The inter-stimulus interval (ISI) will be pseudo-randomized at 12 ± 4 s to minimize anticipatory responses and neural habituation. A total of 35 stimulation trials will be delivered per participant, resulting in an approximate stimulation duration of 7–9 min.

#### EEG acquisition parameters

2.4.3

Continuous EEG will be recorded using a 32-channel system (iRecorder W32, Niantong Intelligent Technology, Shanghai, China). Electrodes will be positioned according to the international 10–20 system, with particular emphasis on fronto-central and parietal regions associated with interoceptive and cognitive processing.

A wet electrode cap based on Ag/AgCl cup electrodes will be used. Conductive gel will be applied to each electrode site to reduce scalp impedance, which will be maintained below 5 kΩ throughout the recording. EEG signals will be sampled at 1000 Hz, with an online bandwidth of 0.1–100 Hz. Signals will be referenced to the bilateral mastoids, with the ground electrode placed at a standard frontal location.

Strict data quality control procedures will be implemented throughout acquisition, including continuous impedance monitoring and artifact inspection.

#### Event synchronization

2.4.4

To ensure temporal alignment between physiological stimulation and neural responses, event synchronization will be implemented via serial communication-based triggering. Specifically, the rectal stimulation device will transmit event markers through a serial interface to the EEG acquisition system at the onset of each balloon inflation.

These event markers will be embedded in real time within the EEG data stream, enabling time-locking of electrophysiological signals to stimulation events for subsequent event-related potential (ERP) and time–frequency analyses.

These trigger signals will be embedded as event markers within the EEG data stream, enabling millisecond-level temporal alignment for subsequent event-related potential (ERP) and time–frequency analyses. This hardware-based synchronization approach ensures high temporal precision and reproducibility of stimulus–response coupling.

All procedures will be conducted under continuous clinical monitoring. Stimulation will be immediately discontinued if any signs of discomfort, autonomic instability, or adverse physiological responses are observed.

### Sample size estimation

2.5

An *a priori* power analysis was conducted using G*Power (v3.1.9.7) based on pilot ERP amplitude data (*n* = 4 per group). Using an independent-samples t-test model, the pilot data yielded a Cohen’s d of 1.13. With a two-tailed *α* = 0.05 and 80% power, the minimum required sample size was estimated at 13 participants per group. To account for potential data loss or dropout, the target sample size was increased to 15 participants per group.

Given the exploratory nature of this study, the sample size is intended to support feasibility assessment and preliminary effect size estimation rather than definitive diagnostic accuracy evaluation. The pilot-based power calculation was performed using a pairwise comparison framework to estimate effect size magnitude; group-level comparisons in the present study are intended for descriptive and exploratory purposes rather than confirmatory hypothesis testing.

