### Data preprocessing and statistical analysis

2.6

EEG data will be preprocessed using EEGLAB (v2024.0) in MATLAB R2024b following a predefined pipeline. Continuous data will be band-pass filtered between 0.1 and 40 Hz and segmented into epochs time-locked to rectal distension onset (−200 to 800 ms). Independent component analysis (ICA) will be applied to identify and remove components associated with ocular, muscular, and cardiac artifacts, based on spatial topography, power spectra, and time-course characteristics.

Event-related potentials (ERPs) will be quantified at predefined fronto-central electrodes. ERP components of interest (N1, P2, and P3) will be defined within fixed latency windows based on prior interoceptive ERP literature (N1: 80–150 ms; P2: 150–250 ms; P3: 250–400 ms). Mean amplitude and peak latency within these windows will be extracted for statistical analysis.

Time–frequency analyses will be conducted using event-related spectral perturbation (ERSP) methods, with baseline normalization relative to the −200 to 0 ms pre-stimulus interval. Power changes in the theta (4–7 Hz) and alpha (8–12 Hz) bands will be quantified.

Group-level comparisons among UWS, MCS, and healthy control participants will be performed using one-way ANOVA for each predefined electrophysiological outcome. *Post hoc* pairwise comparisons will be corrected for multiple testing using the Tukey HSD procedure. Effect sizes (η^2^ or Cohen’s d, as appropriate) will be reported to inform the design of future confirmatory studies. All analyses will be restricted to predefined electrodes, frequency bands, and latency windows to limit multiple comparisons and reduce the risk of false-positive findings.

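### The 80% power in section 2.5 is for one unadjusted t-test; a Tukey-adjusted pair, as planned in section 2.6, has about 74% at 15 per group for the same effect

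*Protocol article*

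**What the plan says.** Section 2.5 (Sample size estimation) takes its effect size from a small pilot, "based on pilot ERP amplitude data (*n* = 4 per group". It states the model and the effect: "Using an independent-samples t-test model, the pilot data yielded a Cohen’s d of 1.13". The result, at a two-sided α of 0.05, is given as "80% power, the minimum required sample size was estimated at 13 participants per group". For data loss or dropout, "the target sample size was increased to 15 participants per group". The section adds that the calculation was pairwise, that the sample size serves feasibility and preliminary effect size estimation, and that group comparisons are exploratory.

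Section 2.6 (Data preprocessing and statistical analysis) fixes a one-way ANOVA across UWS, MCS and healthy controls for each electrophysiological outcome. After that, "pairwise comparisons will be corrected for multiple testing using the Tukey HSD procedure". Section 2.7 lists the group comparisons as secondary exploratory outcomes.

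**The concern.** The test that sets the sample size is not the test that will be run. An unadjusted two-group t-test has a lower critical value than a Tukey comparison among three groups, so power computed for the first overstates power for the second. Section 2.5 does not mention this cost. A non-significant pair could then be read as a miss in a study with 80% power, when the planned procedure has less than that at the same effect.

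Two further features of the calculation matter. The stated minimum of 13 looked slightly low for an exact t-test. And an effect estimated from 4 per group is a weak basis for any power figure.

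**Working it through.** **Inputs.** From section 2.5: d = 1.13 (mean difference in SD units), two-sided α = 0.05, target power 80%, stated minimum 13 per group, target 15, pilot 4 per group. From section 2.6: three groups, one-way ANOVA, Tukey HSD over three pairs. Equal SDs and normal data are assumed throughout.

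**1. The plan's own figure.**
- Normal approximation: n = 2 × [(1.960 + 0.842)/1.13]² = 12.29, rounded up to 13. The stated figure is reproduced.
- Exact t-test: noncentral t with df = 2n − 2 and noncentrality d√(n/2).

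| n per group | Noncentrality | Critical t | Power |
|---|---|---|---|
| 13 | 2.881 | 2.064 | 78.9% |
| 14 | 2.990 | 2.056 | 82.1% |
| 15 | 3.095 | 2.048 | 84.8% |

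The exact minimum is therefore 14. Rounding of d does not explain the gap: 80% at 13 needs d of about 1.145, and any value that rounds to 1.13 gives at most 79.3%. With a minimum of 14, the margin inside 15 is 15 − 14 = 1 per group, not 15 − 13 = 2.

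**2. One Tukey-adjusted pair at the same d.** The critical t is q/√2, where q is the upper 5% point of the studentized range for 3 groups and df = 3(n − 1). The noncentrality is again d√(n/2).

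| n per group | df | Critical t | Power |
|---|---|---|---|
| 13 | 36 | 2.444 | 66.9% |
| 15 | 42 | 2.429 | 74.4% |
| 16 | 45 | 2.424 | 77.7% |
| 17 | 48 | 2.418 | 80.6% |

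Simulation with 100,000 runs per setting agrees (about 67% at 13 and 74.5% at 15). At 15 per group, the d that gives 80% power for a Tukey pair is 1.20.

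**3. Omnibus ANOVA.** Noncentral F with λ = 3nf². With a largest pairwise difference of 1.13, f depends on the third mean:
- Third mean midway: f = 1.13/√6 = 0.461. Power is 69.6% at 13 (λ = 8.30) and 76.6% at 15 (λ = 9.58).
- Two means equal: f = 1.13 × √2/3 = 0.533. Power is 82.2% at 13 (λ = 11.07) and 88.0% at 15 (λ = 12.77).

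The article does not give the position of the third mean.

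**4. What the pilot supports.** With 4 per group, t = 1.13 × √(4/2) = 1.60 on 6 df, p = 0.16. Inverting the noncentral t gives a 95% CI for d of about −0.43 to 2.61. If 1.13 is the uncorrected d (the article does not say), the small-sample correction is 1.13 × (1 − 3/23) = 0.98. Power at 15 would then be 73.8% for the plain t-test.

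**5. What 15 per group gives as precision.** An observed d of 1.13 at 15 per group gives t = 3.09 on 28 df, and a 95% CI for d of about 0.35 to 1.90 by the same method.

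**The case against.** The strongest reply is that the article has already disclosed this. Section 2.5 ties the 80% to a t-test, says the framework is pairwise, and gives feasibility and effect size estimation as the purpose. Section 2.7 makes the group comparisons secondary, and section 2.6 promises effect sizes. Nowhere does the article claim 80% power for a Tukey pair, and no decision hangs on a significance test. All of this stands and lowers the weight of the point. It does not remove it: 13, and hence 15, still come only from the 80% calculation, and the article gives no precision argument although estimation is its stated purpose.

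Three stronger readings are tempting, and the documents do not support them.
- *A reader might infer that 80% also fails for the ANOVA.* It does if the third mean lies midway. If two means coincide, omnibus power is 82.2% even at 13, and the chance that at least one Tukey pair is significant is about 81% at 13 and 87% at 15.
- *A reader might infer that the study is too small for its own t-test.* The shortfall at 13 is 1.1 percentage points, or one participant per group, and the target of 15 gives 84.8%. It falls below 80% only if two or more per group are lost.
- *A reader might infer very low power for UWS against MCS.* A figure of 20% for a Tukey pair at 15 follows only if d = 1.13 is UWS against controls and MCS lies exactly midway. The article states neither. It does not name the pair or ERP component behind d, a detail that a condensed article may leave to the full protocol.

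**Conclusion.** The point holds in limited form. The 80% belongs to one unadjusted pair and does not carry over to a specified Tukey pair. If d = 1.13 is taken as true, power for that pair is 67% with 13 evaluable per group and 74% with all 15, which is 13 and 6 percentage points below 80%. Omnibus power is indeterminate from the article: 77% or 88% at 15 in the two configurations examined. The exact t-test minimum is 14, a correction of one participant per group. All these figures depend on a pilot effect whose confidence interval runs from below zero to beyond 2.6. Severity is moderate, because the comparisons are openly exploratory and no change of design follows.

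**What to change.** Keep 15 per group and reword section 2.5 as follows:
- Give the t-test minimum as 14 per group, with an allowance of one for losses.
- State that at d = 1.13, 15 per group gives 85% power for one unadjusted pair and 74% for one Tukey pair (67% if only 13 per group are evaluable), and that the detectable d for a Tukey pair at 80% power is 1.20.
- Report the pilot 95% CI for d, about −0.43 to 2.61.
- Rest the justification on precision, in line with the stated estimation purpose: an observed d of 1.13 at 15 per group would have a 95% CI of about 0.35 to 1.90.

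The cost is a rewritten paragraph and a less favourable power statement, with no added participants. Keeping an 80% claim for a Tukey pair at this d would instead need 17 evaluable per group, two more than the current target before any allowance for losses.
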